### Postural control

To assess postural control, subjects will be asked to complete three 70-second single limb stance trials with their eyes open and three 45-second single limb stance trials with their eyes closed standing on a force platform embedded in the laboratory floor (Kistler Instruments AG, Winterthur, Switzerland). Only the dominant limb will be used as assessed using the following three tasks (2 out of 3): preferred kicking limb, step up test, and balance recovery[63]. The magnitude of movement and the temporal structure of the center of pressure (COP) trace will be analyzed. The magnitude of movement will be quantified using the path length and 95% ellipse area. The temporal structure will be quantified using the entropic half-life [E(1/2)] of the COP data in the medio-lateral and anterior-posterior direction[64, 65]. Additionally, postural control will be assessed using the Star Excursion Balance Test (SEBT), which has previously been shown to be a reliable and valid measure of postural control[66, 67].

### Kinematics and kinetics

To assess lower extremity running mechanics, subjects will perform 20 over-ground running trials (3.5 m/s ± 15%). Additionally, subjects will perform five minutes of treadmill running at their preferred speed following a five minute walking warm up at 2.5 mph. For the over ground running trials, kinematic data will be collected using an eight high-speed video camera system (Motion Analysis Corporation, Santa Rosa, CA, USA) at a sampling rate of 240 Hz. Previous studies have found that motion capture systems provide results with clinically acceptable errors and relatively high reliability depending on the accuracy of marker placement[68]. Three-dimensional marker traces will be reconstructed using Expert Vision Three-Dimensional Analysis software (Motion Analysis Corporation, Santa Rosa, CA, USA). Kinetic data will be collected simultaneously using a force plate (Kistler Instruments AG, Winterthur, Switzerland) embedded within the laboratory floor with a sampling frequency of 2400 Hz. Retro-reflective markers will be mounted on the rearfoot, shank, and thigh of the right lower extremity and the pelvis to measure three dimensional movements of the ankle, knee, and hip joints[69]. Markers will be placed over the right greater trochanter, medial and lateral knee joint axis, and medial and lateral malleoli in order to define joint centers. Position data from a static neutral trial will be collected in order to define the segment coordinate system. Joint markers will be removed for the running trials. For the treadmill walking, 26 retro-reflective markers were skin-mounted the arms, torso, pelvis, legs and feet. Markers were placed on both sides of the body (three on each foot, three on each shank, three on each thigh, one on each greater trochanter and lateral knee joint center, four on the pelvis) as well as two on the sternum, one on the spine (C7), and one on each shoulder. All biomechanical testing sessions will be completed by the same researcher in order to ensure maximum reliability.

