#### Measurements

Baseline characteristics will be collected for each subject including height, mass, running frequency, running experience, and injury history. Subjects will attend one testing session prior to the training intervention and one testing session immediately following the training intervention (within 9 weeks from baseline) for biomechanical data collection. These testing sessions will involve the collection of isokinetic strength data and the collection of lower extremity running mechanics (kinematics and kinetics) and postural control (dependent variables). Postural control will be assessed as balance deficits have previously been shown to be predictive of future ankle sprains in healthy athletes[57–59].

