#### Analysis

Descriptive statistics of baseline characteristics of the participants in each group will be reported (mean, standard deviation, 95% confidence intervals). These will be presented in tabular form in order to determine if the groups were well balanced with respect to age, mass, height, weekly mileage and running experience[76].

For the isokinetic strength measurements, the peak torque of the three maximal isokinetic contractions will be identified. For postural control, the average entropic half-life in the medio-lateral and anterior-posterior direction will be calculated for the eyes open and eyes closed single limb tasks in the ML and AP direction. Additionally, the average COP 95% ellipse area, average COP path length, and average SEBT reach distance will be calculated. For the over ground running trials, a discrete analysis will be completed using Kintrak software (Human Performance Laboratory, Calgary, Canada) to calculate three-dimensional joint angular displacements, and moments for the ankle, knee and hip joints. Specifically, peak ankle eversion/inversion angle and moment, peak knee ab/adduction angle and moment, peak knee internal/external rotation angle and moment, peak hip ab/adduction angle and moment and peak hip internal/external rotation angle and moment during the stance phase will be calculated. All variables will be normalized to the stance phase of the right foot where heel contact and toe off will be identified as crossing a 15 N threshold. Additionally, a vector-based analysis approach (iterative support vector machine [SVM]) will be used to determine the classification rate of subjects following training as well as to identify the movements that have changed following training using the entire data set rather than discrete time points for the treadmill run[77]. A multivariate linear regression will be used to determine whether the change from baseline to the end of training in each variable for each training group is significantly different from the change found in the control group while controlling for age, gender, and any other baseline differences between the groups.

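### The post-training treadmill run is not tied to the participant's baseline speed, so the classifier could read a speed change as a training effect on mechanics

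*Protocol article*

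**What the plan says.** All places are in the protocol article.

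- **Treadmill test (Kinematics and kinetics).** "subjects will perform five minutes of treadmill running at their preferred speed". The walking warm-up before it has a fixed speed. The measured run does not.
- **Over-ground test (same section).** Twenty trials share one target of 3.5 m/s, with a tolerance of 15% either way. Nothing makes the target differ by session.
- **Timing (Measurements).** "Subjects will attend one testing session prior to the training intervention and one testing session immediately following the training intervention".
- **Treadmill analysis (Analysis).** An iterative SVM is used to obtain a classification rate and to "identify the movements that have changed following training using the entire data set rather than discrete time points for the treadmill run".
- **Regression (Analysis).** Each training arm's pre-to-post change is tested against that of the controls. The adjustment is described as made "while controlling for age, gender, and any other baseline differences between the groups". Speed at the test session is not named.
- **Basis of comparison (Hypotheses).** Every hypothesis is framed as a training group against control, and the mechanics hypotheses cover both running modes.

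**The concern.** The mechanics question is whether eight weeks of training changes how the joints move and are loaded. Running speed is a test condition that can itself alter joint motion. The participants have under a year of running experience and, according to Target population, were chosen partly because they should respond readily to training. A changed preferred speed after eight weeks is therefore plausible. If the treadmill is set to whatever speed feels preferred on the day, a classifier using the whole movement pattern has no means of separating altered technique from altered pace.

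The effect could go either way. The hypotheses predict smaller joint movements and moments in the trained arms. If these rise with speed (an assumption), a trained arm that runs faster could hide a true reduction, and one that runs slower could imitate one. A treadmill speed that was neither recorded nor matched at testing may not be recoverable afterwards.

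**Working it through.** **1. What is fixed and what is free**

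| Test | Speed at baseline | Speed at post-test | Analysis named | Control contrast stated in that sentence |
|---|---|---|---|---|
| Over-ground run | 3.5 m/s ± 15% | same target | discrete peak angles and moments, then regression of change | yes |
| Treadmill run | preferred | preferred; reuse of baseline speed not stated | SVM | no |

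The named covariates are age, gender and baseline differences. A baseline covariate cannot capture a speed change that arises by the second session.

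**2. When a speed change matters**

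Let Δ be an arm's mean pre-to-post speed change and k the outcome's sensitivity to speed.

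- Regression of change against control: speed contributes k × (Δ_training − Δ_control). If all arms speed up equally, this is zero.
- SVM applied to training-versus-control changes: a common speed change again gives no separation between arms.
- SVM applied to pre versus post within an arm: speed contributes k × Δ_training, so even a common speed change counts.

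The Analysis section does not say which form the SVM takes.

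**3. The plan's own sample size, needed for the illustration**

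Sample size gives effect size 0.71, α = 0.05, power 80%, 32 per group and 40 after 20% dropout. Check: n = 2 × (1.960 + 0.842)² / 0.71² = 31.1, rounded up to 32; and 32 / 0.80 = 40. Both figures reproduce. They rest on the centre-of-pressure ellipse area, not on a running variable.

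**4. Illustrative size for one continuous mechanics outcome**

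Two inputs are assumptions, because the article gives neither: d, the between-arm difference in speed change (%), and s, the sensitivity in SD per 10% of speed. With 32 per arm, the standard error of a difference in SD units is √(2/32) = 0.25.

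Shift = (d/10) × s. False-positive rate for an effect that is absent at fixed speed = 1 − Φ(1.96 − shift/0.25) + Φ(−1.96 − shift/0.25).

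Example: d = 5 and s = 0.5 give a shift of 0.25. The rate is 1 − Φ(0.96) + Φ(−2.96) = 17.0%.

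| d | s = 0.2 | s = 0.5 | s = 1.0 |
|---|---|---|---|
| 0% | 5.0% | 5.0% | 5.0% |
| 2% | 5.3% | 6.9% | 12.6% |
| 5% | 6.9% | 17.0% | 51.6% |
| 10% | 12.6% | 51.6% | 97.9% |

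This describes a between-arm comparison of means. It does not describe the SVM's classification rate, for which the article gives nothing to compute from.

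**5. The over-ground window**

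Limits: 3.5 × 0.85 = 2.975 m/s and 3.5 × 1.15 = 4.025 m/s. Width 1.05 m/s; ratio 4.025 / 2.975 = 1.353.

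Suppose trial speeds scatter uniformly and independently in the window (assumption). The SD per trial is 1.05/√12 = 0.303 m/s. The SD of the pre-to-post change in a 20-trial mean is 0.303 × √(2/20) = 0.096 m/s, which is 2.7% of target. At s = 0.5 the added variance is (0.274 × 0.5)² = 0.0188 SD², and power at 32 per arm for an effect of 0.71 moves from 81.1% to 80.3% (80.9% at s = 0.2, 78.2% at s = 1.0). Random spread within the window is a minor matter.

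**The case against.** The strongest case against has four parts.

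- **The text does not say that speed is chosen afresh.** It says only that the run is at preferred speed. The laboratory may carry the baseline setting forward, and a full protocol not shown may say so. This stands as far as it goes: a reader might infer that speed is not held constant, but the article supports only that it is not required to be. The section does, however, give marker counts, sampling rates, the warm-up speed and a same-tester rule, and the speed of the measured run is as basic a condition as any of these.
- **The control group removes the main mechanism.** If novices in all arms get faster, the regression of change against control cancels it. This stands. It does not cover speed changes that differ by arm, which are conceivable: Table 2 has the balance arm doing hops, jumps and lunges, while Table 1 gives controls light aerobic work and stretching. Nor does it clearly cover the SVM. The Hypotheses section makes the control contrast the basis of every hypothesis, which favours a controlled reading of the SVM, but the Analysis sentence does not carry that contrast through.
- **Over-ground speed has a common target.** This stands. A reader might take the 35% gap between the ends of the window as a measure of the problem, or infer a material loss of power. Neither is supported. The gap requires a whole session at one end and the next session at the other, and random spread costs under one percentage point of power at the middle sensitivity. Converting the gap into a change in moments would also need an assumed exponent. The article describes force measurement only for the over-ground runs, so such a figure would not size the treadmill problem.
- **Omitting speed from the main model is not an error.** This stands. Speed change is measured after randomisation and may itself result from training, so conditioning on it changes the question.

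**Conclusion.** The point holds for the treadmill test, in limited form. The protocol does not require the post-training run to be at the baseline speed, and the classifier applied to that run has no stated handling of speed. A speed change that differs between arms could be read as an effect of training on mechanics. So could any speed change at all, if the classifier separates pre from post without control.

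The size cannot be derived from the article. The rates in the working, from 5.3% to 97.9% over the non-zero differences tried, rest wholly on assumed speed differences and sensitivities, and the rate stays at 5% if speed change does not differ between arms.

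A reader might go further and conclude that the randomised comparison is invalid. It is not: an arm-specific speed change would itself be a consequence of allocation. What becomes unclear is whether mechanics changed at a given speed, which is the question the hypotheses pose. For the over-ground trials, the only remaining risk is a systematic drift in speed that differs by arm, and nothing in the article shows one.

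**What to change.** 1. **Treadmill.** Record each participant's preferred speed at baseline and set the treadmill to that same speed at post-test.
2. **Classifier.** State that it is applied to training-versus-control changes, in line with the Hypotheses section, so that changes common to all arms are not credited to training.
3. **Over ground.** Keep the 3.5 m/s target. Record the speed of each trial and report mean speed by arm and session.
4. **Adjustment.** Put the pre-to-post change in speed into a supporting analysis only, because it is measured after randomisation. Leave the main regression as it is.

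The cost is one instruction to the tester, one sentence on the classifier, one table of speeds and one supporting model. The downside is that the post-test treadmill speed may no longer be the runner's preferred one, so the test would then describe mechanics at a matched speed rather than at the speed the runner would choose.

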#### Hypotheses

All hypotheses are made based on comparisons between each of the training groups and the control group.Isolated ankle strengthening will increase ankle isokinetic strength but not strength at the knee or hip joints.Isolated ankle strengthening will significantly decrease joint movements and joint moments in the frontal and transverse planes at the ankle during over ground and treadmill running.Functional balance training will significantly increase ankle and knee and hip isokinetic strength.Functional balance training will significantly decrease joint movements and joint moments in the frontal and sagittal planes at the ankle, knee and hip joints during over ground and treadmill running.Functional balance training will significantly reduce the center of pressure movement magnitude, increase the regularity of the center of pressure time series and improve performance on the Star Excursion Balance Test.Injury rates will be lower for the functional balance training group and the isolated ankle strengthening group compared to the activity matched control group.

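### Two hypotheses predict lower joint moments on the treadmill, where no force measurement is described, and treadmill movements have no defined comparison with control

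*Protocol article*

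**What the plan says.** All places are in the protocol article.

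- **Hypotheses, second (strength versus control).** Isolated ankle strengthening is expected to "decrease joint movements and joint moments in the frontal and transverse planes at the ankle during over ground and treadmill running".
- **Hypotheses, fourth (balance versus control).** Functional balance training is expected to "decrease joint movements and joint moments in the frontal and sagittal planes at the ankle, knee and hip joints during over ground and treadmill running". The section opens by stating that every hypothesis compares a training group with the control group.
- **Kinematics and kinetics, over-ground set-up.** Camera motion capture is paired with force recording: "Kinetic data will be collected simultaneously using a force plate (Kistler Instruments AG, Winterthur, Switzerland) embedded within the laboratory floor".
- **Kinematics and kinetics, treadmill set-up.** The task is that "subjects will perform five minutes of treadmill running at their preferred speed". The instrumentation described is a marker set: "For the treadmill walking, 26 retro-reflective markers were skin-mounted the arms, torso, pelvis, legs and feet". No treadmill force instrument is mentioned.
- **Analysis, over-ground trials.** The discrete peak angles and moments for ankle, knee and hip are calculated for these trials.
- **Analysis, treadmill run.** An iterative support vector machine is to give a classification rate and to identify which movements changed after training, "using the entire data set rather than discrete time points for the treadmill run".
- **Analysis, group comparison.** A regression compares the change in each variable between each training group and control, adjusted for age, gender and baseline differences.

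**The concern.** A joint moment during stance, obtained as this article describes, needs the ground reaction force under the foot. A plate in the laboratory floor cannot record contacts made on a treadmill. The hypotheses therefore promise a treadmill result that the described measurements cannot deliver.

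A second, weaker gap concerns treadmill movements. The hypotheses predict a decrease, in named planes, relative to control. The classifier output is described only as what changed after training, with neither a direction nor a control contrast. If the classifier separated before from after within one group, controls could show separation too, from marker re-placement or simple retesting.

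Two reporting problems could follow. Over-ground moment results might be presented as confirming the treadmill claims, or those claims might drop out without explanation. A classification rate might also be read as a training effect when no comparison with control has been made.

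**Working it through.** **1. The plan's only sample-size figure, to see whether it depends on this point.** The Sample size section gives an effect size of 0.71, α = 0.05, power 80%, 32 per group, and 40 after 20% dropout. Sidedness is not stated; two-sided is assumed here.

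- n per group = 2 × (1.96 + 0.8416)² / 0.71² = 15.70 / 0.5041 = 31.1, rounded up to 32.
- With dropout: 32 / (1 − 0.20) = 40.

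The figure reproduces. It rests on the 95% ellipse area of the centre of pressure, which is not a running variable, so the treadmill problem does not touch it.

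**2. Hypothesis components set against data and analysis.** Each of the two hypotheses covers two outcomes (movements, moments) in two conditions (over ground, treadmill): 2 × 2 × 2 = 8 components in all.

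| Component (in each hypothesis) | Data described | Between-group analysis described |
|---|---|---|
| Over-ground movements | Yes, cameras | Yes, peak angles in the regression |
| Over-ground moments | Yes, cameras and floor plate | Yes, peak moments in the regression |
| Treadmill movements | Yes, markers | None defined; classifier only |
| Treadmill moments | No force source | None |

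Across the two hypotheses, 4 of 8 components have data and a group test, 2 of 8 have data without a defined group test, and 2 of 8 have neither. The over-ground entries hold for the planes covered by the listed peak variables. Those variables are frontal and transverse, whereas the fourth hypothesis names the sagittal plane; that is a separate matter.

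**3. Can the treadmill markers yield joint movements?** The section lists, on each side, three markers on the foot, three on the shank, three on the thigh, one at the greater trochanter and one at the lateral knee, plus four on the pelvis: 2 × (3 + 3 + 3 + 1 + 1) + 4 = 26. Adding two on the sternum, one at C7 and one on each shoulder gives 26 + 2 + 1 + 2 = 31, against a stated total of 26 that is said to include the torso and arms. On either count, three markers per leg segment and four on the pelvis are enough for ankle, knee and hip kinematics. The marker sentence says walking, but the Analysis section applies the classifier to the treadmill run, so I take the same markers to be worn for running.

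**4. Does any treadmill variable reach the regression?** The regression covers each variable, but the only discrete running variables named belong to the over-ground trials. For the treadmill, the text names a classification rate and a set of changed movements. A classification rate describes a group of runners. It is not a change score for each runner, so it cannot be entered as an outcome in that regression without further definition.

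**The case against.** The strongest reply is that a journal article condenses its methods. It names no separate camera system or sampling rate for the treadmill either, so silence about treadmill force is weaker evidence than an explicit statement. The control contrast is also declared for all hypotheses at the head of the Hypotheses section, and how classifier output enters it could be set out in a fuller document or in the cited method. This stands in part. The treadmill may have force sensors that the article does not mention, and the fix allows for that. But the article does not merely stay silent: it ties kinetics to the over-ground capture and moment calculation to the over-ground trials, while claiming treadmill moments in two hypotheses. An analysis plan cannot supply forces that were not recorded.

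Four stronger readings are tempting, and the document does not support them:

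- **The whole treadmill part of both hypotheses is untestable.** It is not. The markers can give joint kinematics, and the classifier is also meant to identify the movements that changed.
- **The stance rule is contradictory.** The statement that "heel contact and toe off will be identified as crossing a 15 N threshold" closes the over-ground discrete analysis, and the treadmill classifier is introduced only afterwards. Read in order, the force threshold applies to the over-ground variables.
- **Treadmill speed is chosen afresh at each session.** The article says only that speed is the preferred one. It does not say whether the baseline speed is reused, so a speed change is a possibility and not a stated feature.
- **The classifier will overfit.** That depends on how accuracy is validated, which the article does not state and may properly leave to an analysis plan.

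It is also fair to say that marker re-placement affects all groups alike and that one researcher runs all sessions. A randomized comparison with control would deal with that concern, provided the classifier analysis actually makes the comparison.

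**Conclusion.** The point holds in this form. The treadmill joint-moment component of the second and fourth hypotheses cannot be tested with the measurements and analysis described. The treadmill joint-movement component is measurable but has no defined between-group endpoint: no treadmill variable is named for the regression, and the classifier is not stated as a training-versus-control test of a decrease in a named plane.

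In size, this affects two of the six hypotheses: two of their eight components lack data, and two more lack a defined group test. Severity is moderate. The moment claims can still be tested over ground, the sample size rests on a balance measure, and the injury outcome uses no treadmill data.

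The conclusion assumes that the treadmill has no force measurement beyond what the article describes, and that the marker set described under walking is also used for the treadmill run. If treadmill force was recorded, the first part becomes a matter of describing it and adding treadmill moments to the analysis.

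**What to change.** 1. Restrict the joint-moment wording of the second and fourth hypotheses to over-ground running. If treadmill force measurement exists, describe it and name the treadmill moment variables instead.
2. Name treadmill peak joint angles for the planes in the hypotheses. Compute them from the planned markers, detect foot contact from the markers, and enter each runner's change in the regression already planned against control.
3. State the classifier contrast as training versus control, applied to each runner's post-minus-pre data. Validation details can go in the analysis plan.
4. Use the same treadmill speed for each runner at both sessions, and record it.

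The cost is a wording change, some extra processing of marker data already planned, and a written record of speed; no procedure is added. There is one small downside: the post-test speed may differ slightly from the speed the runner would by then prefer.
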